**Conclusions:**

The complexities inherent in care home research has resulted in the under representation of this population in research trials. The results of this feasibility trial will be used to inform the development and design of a future cluster randomised controlled trial to compare food-based intervention with prescribed oral nutritional supplements (ONS) in the treatment of malnutrition within the care home population.

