No systematic review to date has made any specific conclusions regarding nutritional interventions for the treatment of malnutrition in the elderly care home setting. There is a tendency to avoid research in care homes, because of the challenges and methodological issues involved in conducting research in this setting [24]. Many research studies specifically exclude care home residents on the basis that their inclusion would present the research team with ethical and practical difficulties [25]. Studies, which have been conducted in the care home setting often, include dementia and immobility within the exclusion criteria [26–28], despite these being well-established risk factors for malnutrition. As a result, knowledge on the actual effectiveness of nutritional intervention in this vulnerable population is limited and the clinical applicability of findings to those care home residents most at risk of malnutrition is often questionable. With an ageing population set to increase in the coming years, care homes will play an increasingly vital role in supporting and caring for older people. The lack of evidence to support the best practice has led to recommendations for more studies to be conducted in the care home setting [29] and provides an opportunity to bring new ideas to the field.

To enable the efficacy of food-based interventions to be compared with ONS intervention within a care home population, an adequately powered RCT is required, using interventions that are equivalent in energy and protein composition, alongside a comparative routine care arm. The Medical Research Council (MRC) framework [30] explicitly recommends that complex interventions should be investigated using preliminary studies, prior to evaluation in a RCT, in order to optimise the trial design, to define the outcomes and to ensure feasibility. Given the expected complexities of care home research, a feasibility trial for a multi-centre cluster RCT was proposed, to explore trial design, staff, and resident acceptability and to provide data to estimate the parameters required to design a definitive RCT.

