The trial will have a number of quantitative objectives:To assess how many care homes for the elderly accept the invitation to participate in a nutritional intervention feasibility trialTo determine whether the eligibility criteria for malnourished care home residents are too open or too restrictive, by estimating feasible eligibility and recruitment rateTo assess retention of care homes and residents, by estimating 3- and 6-month follow-up ratesTo investigate the acceptability of nutrition support interventions to malnourished care home residents, in terms of compliance, and to care home staff in terms of adherence to the intervention scheduleTo determine the acceptability and feasibility (and factors influencing this) of the different outcome measures as methods to measure efficacy of nutritional interventions within a definitive trialTo investigate the completion and accuracy of nutritional screening and questionnaire completion by care home staffTo determine how many malnourished care home residents are able to participate in PROMs and to complete the questionnairesTo measure key outcome domains (for completion rates, missing data, estimates, variances and 95% confidence intervals for the difference between the intervention arms) for malnourished care home residents including physical outcome measures and PROMsTo collect and synthesise data, from which to estimate the intracluster correlation coefficient (ICC) and inform the sample size of a definitive trial

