#### Statistical analyses

The detailed statistical approach will be published subsequently with the results of the trial.

All continuous data will be tested for normality using Kolmogorov-Smirnov. Categorical variables will be compared between intervention arms at baseline using the chi-square test. Mean changes in continuous outcome measures, such as nutrient intake and anthropometric parameters, will be calculated at 3 and 6 months, along with 95% confidence intervals. Group mean changes will be compared between each of the dietetic-led intervention arms and the standard care arm, using the independent-sample *t*-test for normally distributed data and the Mann-Whitney *U* test for data, which violates normality. Where sensitivity to change is suggested from the 95% confidence interval, the independent-sample *t*-test will be used to compare food-based intervention with ONS intervention for that particular outcome measure.

Completion rates and missing data will be summarised for all outcome assessments, along with estimates and variances, to determine the most appropriate primary outcome measure for a definitive trial. If an appropriate primary outcome measure is identified within this trial, the data collected will help to inform the calculation of the intracluster correlation coefficient (ICC), the design effect (DE) and the effective sample size for a definitive trial.

where *(m × k)* is the total number of subjects in a clustered trial, *m* is the number of subjects in a cluster and *k* is the total number of clusters.

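### The food-based versus ONS comparison is run only where an unspecified 95% confidence interval suggests sensitivity to change, although the protocol's own objective promises that difference with its interval unconditionally

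*Protocol article*

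**What the plan says.** All references are to the protocol article.

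- **Statistical analyses, unconditional parts.** Mean changes in continuous outcomes "will be calculated at 3 and 6 months, along with 95% confidence intervals". Food-based intervention and ONS are each then set against standard care, with no precondition, by t-test or, where normality fails, by Mann-Whitney. Completion, missingness, estimates and variances are to be summarised for every outcome assessment.
- **Statistical analyses, conditional part.** Food-based intervention and ONS are compared with each other, outcome by outcome, only "Where sensitivity to change is suggested from the 95% confidence interval". A t-test is the sole method named for this step. The sentence does not say which interval is meant (within an arm or between arms), which arm or visit counts, or what qualifies as a suggestion.
- **Aims and objectives, quantitative objectives.** For key outcome domains, physical and patient-reported, the trial is to provide estimates, variances and "95% confidence intervals for the difference between the intervention arms". No condition is attached.
- **Descriptive statistics.** Because testing needs a powered sample, the analysis is confined to description and exploratory estimation.
- **Abstract (Conclusions) and Background.** The results are to inform a definitive trial "to compare food-based intervention with prescribed oral nutritional supplements (ONS) in the treatment of malnutrition within the care home population". The Background gives the same reason for it: "To enable the efficacy of food-based interventions to be compared with ONS intervention within a care home population", with a routine care arm alongside.

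**The concern.** The one contrast made to depend on the data is the one the definitive trial is being built around. Whether an outcome moves against standard care, or from baseline, does not settle whether the food-based versus ONS interval is needed. Two arms with equal benefit need that interval as much as two arms with unequal benefit.

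A condition read off a 95% interval acts much like a significance filter, in a sample the article itself treats as unsuited to testing. Two things follow if it is applied as written. For some outcomes the planned difference and its interval will not appear. Where they do appear, they come from samples chosen because at least one dietetic arm looked extreme, so the differences tend to be too large.

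A smaller inconsistency is that the conditional comparison is fixed as a t-test, although the preceding sentence sends non-normal data to Mann-Whitney.

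**Working it through.** **1. The plan's own figure.** There is no power calculation. The size per home reproduces: 29 × 0.30 = 8.7 (stated 9) and 72 × 0.42 = 30.2 (stated 30). Over six homes this gives about 52–54 to 180, against a stated 50 to 180, which is close enough for this purpose.

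**2. Residents per arm (three arms).** 50/3 ≈ 17 and 180/3 = 60. At the 65% retention criterion, 16.7 × 0.65 ≈ 11 and 60 × 0.65 = 39.

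**3. Assumptions, because the article gives no effect size or ICC.** Change scores have SD 1, residents are independent, and one visit is considered. Two readings of the condition are examined:

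- Reading A: the 95% CI of either dietetic arm against standard care excludes zero, i.e. |x̄ₖ − x̄ₛ| > t(0.975, 2n−2) × √((sₖ² + sₛ²)/n) for k = food-based or ONS.
- Reading B: the 95% CI for mean change within either dietetic arm excludes zero, i.e. |x̄ₖ| > t(0.975, n−1) × sₖ/√n.

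**4. How often the contrast is dropped, with a true 0.5 SD in both dietetic arms.** For a single contrast with standard care, power is 0.20, 0.29 and 0.78 at 11, 17 and 60 per arm. Either arm can satisfy reading A, and the two contrasts share the standard care arm, so the joint probability was simulated. For reading B the two arms are independent and the loss is (1 − p)², with p ≈ 0.325 at 11 and 0.49 at 17: 0.675² ≈ 0.46 and 0.51² ≈ 0.26.

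| Per arm | A: condition met | A: dropped | B: condition met | B: dropped |
|---|---|---|---|---|
| 11 | 31% | 69% | 54% | 46% |
| 17 | 43% | 57% | 74% | 26% |
| 60 | 90% | 10% | over 99% | under 1% |

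If either visit may satisfy the condition (assumed correlation 0.5 between visits), A is met in 47% (11 per arm) or 61% (17 per arm), so 53% or 39% are dropped. B is met in 73% or 89%, so 27% or 11% are dropped.

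**5. What the condition does to the contrasts that survive (reading A).**

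- True effects 0.2 SD (food-based) and 0.5 SD (ONS), true difference −0.30. Without the condition the estimate averages −0.30. With it, the average is about −0.46 at 11 per arm (repeat runs fall between −0.46 and −0.47) and −0.36 at 39 per arm.
- No effect in any arm. The condition is met about 9% of the time. Among those samples the food-based versus ONS t-test is significant in about 20%, not 5%, and the mean absolute difference is about 1.6 times too large.
- If clustering is present but ignored (assumed ICC 0.05–0.10, 10 or 38 per arm), the condition is met with no true effect in 14%–41% of samples.

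**6. Against the objective.** Whether the objective's wording covers all three arms or only the two dietetic ones, food-based versus ONS is included. The objective attaches no condition and the analysis section does, so both cannot be followed.

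**The case against.** The case for leaving the text alone has real weight.

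- **Little is truly lost.** Arm-level mean changes with intervals, and variances for every outcome, are unconditional. A reader could subtract two arm means and build an approximate interval. This stands. It limits the point to the planned contrast and its interval. One might infer that variances or the ICC inputs go missing as well; they do not depend on the condition.
- **The primary outcome is not chosen this way.** A reader might infer that the condition biases the choice of the definitive primary outcome and its planning effect. The article bases that choice on completion, missing data, estimates and variances across all outcomes, and nowhere uses the conditional difference as a planning effect. That inference is not supported.
- **The size depends on the reading.** Power for one contrast at one visit would suggest that 70%–80% of moderate effects lose their comparison. Two arms, and possibly two visits, can satisfy the condition, so that overstates the loss. The phrase may also refer to within-arm responsiveness, which gives the smaller figures. Similarly, 1 − 0.95²⁸ = 0.76 for at least one false signal among 28 intervals (seven outcomes, two arms, two visits) assumes independence. Weight and BMI, or energy and protein from the same charts, plainly are not independent, so it is only an upper bound.
- **The work is exploratory, and the detailed approach is deferred to the results paper.** This lowers the severity. A fuller plan may define the interval, and the bare t-test may be shorthand. However, deferral does not withdraw a rule the article states, and any definition would still leave the comparison conditional.

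**Conclusion.** The point holds in a limited form. As written, the rule makes the food-based versus ONS comparison conditional on the data. That contradicts the article's own objective and sits badly with its restriction to estimation.

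The harm is greatest near the recruitment target of at least 50 residents, where the planned contrast would be dropped in roughly a quarter to two thirds of cases under a moderate effect, depending on the reading. It is small near 180 residents before attrition. These figures rest on assumed effects of 0.5 SD (or 0.2 and 0.5 SD), independent residents and a single visit; a second visit lowers the losses. The inflation of surviving differences likewise shrinks as the arms grow. The Mann-Whitney inconsistency is minor.

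This should be changed, but it does not threaten the feasibility and acceptability outcomes, which are the trial's primary purpose.

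**What to change.** Delete the condition. For every continuous outcome at 3 and 6 months, report three contrasts whatever the result: food-based versus standard care, ONS versus standard care, and food-based versus ONS. Give each as a mean difference with arm SDs and a 95% CI that allows for clustering by home. Apply one rule for non-normal data to all three. Keep the choice of the definitive primary outcome on completeness, acceptability and variance, and say explicitly that it does not depend on whether an interval excludes zero.

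The cost is a sentence of text and one extra column per outcome table, with no new data. The intervals will be wide: with two homes per arm, a home-level contrast between two arms has only 2 + 2 − 2 = 2 degrees of freedom. That is an honest statement of what six homes can show, and the article should say so.

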### Phase 2 qualitative analysis

The qualitative data will be analysed using the Krueger [45] and Ritchie and Spencer [46] framework analyses, assisted by the NVivo computer programme as required. The process of data analysis will begin during data collection, through the effective facilitation of the interview and focus group discussions, complemented by observational notes. Following data collection, the dietitian researcher will transcribe the audio tapes and identify major themes.

Concepts, ideas and short phrases identified within the text will be used to develop categories and a thematic framework. Once a framework has been developed, the data will be indexed using a process of sorting, highlighting and arranging quotes to make comparisons between and within cases. Once indexed, the quotes will be re-arranged under the appropriate thematic content. The final stage of analysis will be mapping and interpreting the data, identifying links between the quotes and exploring and explaining patterns of association.

The qualitative analysis will be interpreted alongside the quantitative feasibility and acceptability findings, to inform the design of the future definitive trial.

## Discussion

Careful planning to overcome the challenges of UK care home-based research is essential to prepare and design a cluster randomised trial of adequate size and quality to evaluate the efficacy of nutrition support interventions. The complexities inherent in care home research has resulted in the under representation of this population in research trials. Challenges can include recruitment difficulties due to physical and/or cognitive impairments [24, 47], the consent process [24, 47] and the high attrition rates of older people from research [24]. Data collection within the busy schedule of care homes, along with poor staff compliance with the intervention and data protection protocols [24], can also pose issues for researchers. In previous nutritional intervention studies conducted within the care home setting, methodological limitations have been acknowledged, for example, difficulties with receipt of consent [14, 48], and drop-out rates of 25%–33% [27, 49, 50]. Before an adequately powered, high-quality cluster randomised controlled trial comparing nutritional interventions for malnutrition in the care home setting can be designed and conducted, a feasibility trial is being completed to provide the necessary information.

### Other practical issues involved in conducting the trial

#### Adverse events (AEs) and serious adverse events (SAEs)

This trial was considered to be low risk. The nutritional interventions are well established and are currently in use to treat malnutrition in the care home population. Expected adverse events included:

A risk of mild side effects in response to a fortified diet or prescribed ONS, including diarrhoea, bloating, nausea and satiety.

No other risks were anticipated, and therefore it was considered reasonable to collect only targeted dietary intervention-related AEs and only serious adverse events (SAEs) requiring hospital admissions that were due to avoidable malnutrition or dehydration.

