### Safety considerations

#### Risk of re-feeding syndrome on initiation of an energy-fortified diet or ONS

Those at risk of re-feeding syndrome were identified through routine ‘MUST’ screening, if they had any of the following: a BMI of less than 16 kg/m [2], weight loss of greater than 15% over the last 3 to 6 months, no or negligible dietary intake for ten consecutive days [9]. If any resident was identified as being at risk of re-feeding syndrome at baseline, nutritional intervention was commenced cautiously, at 10 kcal/kg/day, increasing to provide the additional 600 kcal and 20–25 g protein by day 7. The dietitian also requested that the GP monitors electrolytes and glucose. This procedure is in line with usual, standard dietetic practice and national guidance [9].

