#### Deteriorating swallow function (dysphagia) and an increased risk of aspiration

If dysphagia was identified or suspected during the 6-month intervention duration, by the care home staff or the primary researcher, this prompted a referral to the Speech and Language Therapy (SaLT) team, as per usual standard practice.

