#### Reporting of adverse events and serious adverse events

The care home staff were required to inform the primary researcher if any AEs/SAEs relating to a resident’s malnutrition and/or its treatment were identified, through the completion and faxing of an adverse event form. The incidence and frequency of AEs were recorded at 3 and 6 months of intervention duration. Death from any cause was reported by care home staff on an AE form and faxed to the primary researcher.

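### The SAE rule rests on a statement that no risks beyond mild side effects were anticipated, but the protocol's own safety section names re-feeding syndrome and aspiration, and a non-fatal admission for either is not an SAE as defined

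*Protocol article*

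**What the plan says.** Under Adverse events (AEs) and serious adverse events (SAEs), the protocol article calls the trial low risk and gives one group of expected events: "A risk of mild side effects in response to a fortified diet or prescribed ONS, including diarrhoea, bloating, nausea and satiety". It continues: "No other risks were anticipated, and therefore it was considered reasonable to collect only targeted dietary intervention-related AEs". The same sentence limits the serious category to "only serious adverse events (SAEs) requiring hospital admissions that were due to avoidable malnutrition or dehydration".

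Under Safety considerations, two of the subsections are headed "Risk of re-feeding syndrome on initiation of an energy-fortified diet or ONS" and "Deteriorating swallow function (dysphagia) and an increased risk of aspiration". The first defines which residents are at risk and provides for a modified start to the intervention in them. It adds: "The dietitian also requested that the GP monitors electrolytes and glucose". The second sends suspected dysphagia arising during the six-month intervention to the Speech and Language Therapy team. Under Descriptive variables, the baseline form records re-feeding risk, with its risk factors, and any diagnosis of dysphagia.

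Reporting of adverse events and serious adverse events asks staff to notify the primary researcher if AEs or SAEs relating to a resident's "malnutrition and/or its treatment were identified". Deaths from any cause also go on an AE form. The joint TSC/DMC meets every three months for safety monitoring.

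**The concern.** The narrow SAE rule is presented as following from the absence of other anticipated risks. The protocol does anticipate other risks: it names them, screens for one of them, and sets out what happens when they are found. Once the premise goes, the rule has no stated justification.

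The rule also has a practical effect. It requires an admission and a particular cause, "requiring hospital admissions that were due to avoidable malnutrition or dehydration". That describes failure to nourish or hydrate. A serious complication of starting nutritional treatment, or an aspiration event, is a different kind of cause. If a resident were admitted for one of these and survived, the protocol gives no basis for calling the event an SAE.

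Two things are at stake. The first is whether the three-monthly TSC/DMC review can recognise serious events of the kinds the protocol itself names. The second is whether the definitive trial, which this study is meant to inform, takes over a low-risk description and an SAE definition whose stated basis does not hold.

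**Working it through.** No arithmetic applies. The documents give no rate for re-feeding complications, aspiration or hospital admission, so the check is a comparison of sections.

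1. **Is the premise consistent with the rest of the protocol?** The AE section expects diarrhoea, bloating, nausea and satiety, all mild, and says nothing else was anticipated. Safety considerations names re-feeding syndrome and ties it to starting a fortified diet or ONS. It sets criteria for being at risk and asks for biochemical monitoring. Descriptive variables puts the risk on the baseline form. Safety considerations also names an increased risk of aspiration. The premise is contradicted.

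2. **Does the restriction depend on the premise?** Yes. The two are joined by the words *and therefore*, and no other reason is tied to the restriction. The surrounding text says only that the interventions are well established and in current use.

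3. **Would an admission for a named risk meet the SAE rule?** The rule has two conditions: hospital admission, and cause equal to avoidable malnutrition or dehydration.
   - Non-fatal re-feeding admission: the first condition is met. The second is not met as written, because the cause is a complication of starting nutrition.
   - Non-fatal aspiration admission: the first condition is met, the second is not.

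4. **Are susceptible residents in the trial?** The exclusion criteria for residents list neither re-feeding risk nor dysphagia, and the baseline form records both. The question is therefore not hypothetical for this population.

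5. **Would the event be lost altogether?** Not necessarily. Three routes remain:
   - the AE section still collects dietary intervention-related AEs;
   - the reporting section covers events related to malnutrition and/or its treatment;
   - death from any cause is reported.

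   A re-feeding admission could arrive by either of the first two routes. An aspiration admission could do so only if staff judged it related to malnutrition or its treatment. What is shown is a failure of classification and counting for non-fatal serious events. Loss of the data is not shown.

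6. **Do the two reporting scopes agree?** The reporting section applies its wider wording to AEs and SAEs alike. The AE section's SAE rule does not mention treatment. The two can be reconciled only by reading the reporting wording as a loose union of intervention-related AEs and malnutrition-related SAEs. Even on that reading, a serious treatment harm is an AE and not an SAE.

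7. **Can a direction of bias between arms be derived?** No. The SAE rule is aimed at under-nutrition, whereas the AE rule is aimed at effects of dietary intervention, so the two work in opposite directions. Under Standard care arm, residents in all six homes receive standard care, and those allocated to standard care only receive an energy-enriched diet. Re-feeding on a fortified diet is therefore not confined to the two dietetic intervention arms.

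**The case against.** The strongest reply is that this is a matter of labels. Intervention-related AEs are collected, the reporting instruction mentions treatment, and all deaths are notified, so a serious re-feeding event would probably reach the primary researcher. The planned descriptive statistics already summarise mortality, adverse events, withdrawals and resource use, partly to show imbalance between arms. Safety is neither a primary nor a secondary outcome, and the analysis is descriptive and exploratory. This reply stands to the extent that it rules out saying these harms go unreported. It does not restore the premise, and it does not make a non-fatal re-feeding or aspiration admission an SAE.

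A second reply concerns aspiration. The protocol describes swallowing decline during the intervention period and does not attribute it to the intervention. That is correct. Aspiration is a serious risk the protocol names, but the text does not make it a treatment harm. Re-feeding, which the protocol links explicitly to starting the diet or ONS, is the firmer example and is enough by itself.

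A third reply is timing. Recruitment to phase 1 closed in December 2013. Six months of intervention from then runs to about June 2014, and the account of phase 2 gives a July 2014 start. A change to the AE form may come too late for phase 1. This affects what the remedy can be, but the inconsistency remains.

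A reader might also infer that the TSC/DMC would see none of the serious treatment events and that the safety comparison is tilted towards the intervention arms. The document does not support either inference. Other reporting routes exist, the AE and SAE limits pull in opposite directions, standard care also enriches the diet, and the protocol does not say which data the committee receives.

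**Conclusion.** The point holds as an internal contradiction with a definite but limited consequence. The stated reason for restricting SAE collection is untrue on the protocol's own text. Under the rule as written, a non-fatal hospital admission for re-feeding syndrome or aspiration is not classed or counted as an SAE.

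Its numerical size is unknown. No event rates are given, so neither the number of events affected nor the direction or amount of any distortion between arms can be worked out. Assigning a percentage of residents would mean inventing the event count.

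The conclusion assumes that the cause of an admission is read literally. If staff attributed a re-feeding admission to the underlying malnutrition, it might be counted, but that would turn the SAE count on a causal judgement by staff who are not blinded to allocation.

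**What to change.** Reconcile Safety considerations with the two adverse event sections:

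- Remove the statement that no other risks were anticipated.
- List re-feeding complications and aspiration among the targeted events on the AE form.
- Define reportable SAEs to include hospital admissions whatever the attributed cause. At the least, include those related to malnutrition or its treatment, so that the SAE definition matches the reporting instruction.
- Give these counts to the three-monthly TSC/DMC review by arm. Summaries by arm are largely planned already, so what changes is the scope of capture.

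If phase 1 collection is already complete, review admissions retrospectively from care home records where possible, report the narrow SAE scope as a limitation, and carry the corrected definition into the definitive protocol. The healthcare resource usage questionnaire could serve as a cross-check if it itemises admissions, which the article does not say.

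The cost is revised wording, an amended AE form and slightly more reporting by care home staff. A retrospective review adds some record checking in six homes. None of this changes how residents are treated.
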